## Abstract

**Background:** Transcranial direct current stimulation (tDCS) and therapy-based virtual reality (VR) have been investigated separately. They have shown promise as efficient and engaging new tools in the neurological rehabilitation of individuals with cerebral palsy (CP). However, the recent literature encourages investigation of the combination of therapy tools in order to potentiate clinic effects and its mechanisms.

**Methods:** A triple-blinded randomised sham-controlled crossover trial will be performed. Thirty-six individuals with gross motor function of levels I to IV (aged 4–14 years old) will be recruited. Individuals will be randomly assigned to Group A (active first) or S (sham first): Group A will start with ten sessions of active tDSC combined with VR tasks. After a 1-month washout, this group will be reallocated to another ten sessions with sham tDCS combined with VR tasks. In contrast, Group S will carry out the opposite protocol, starting with sham tDCS. For the active tDCS the protocol will use low frequency tDCS [intensity of 1 milliampere (mA)] over the primary cortex (M1) area on the dominant side of the brain. Clinical evaluations (reaction times and coincident timing through VR, functional scales: Abilhand-Kids, ACTIVLIM-CP, Paediatric Evaluation of Disability Inventory-PEDI- and heart rate variability-HRV) will be performed at baseline, during, and after active and sham tDCS.

**Conclusion:** tDCS has produced positive results in treating individuals with CP; thus, its combination with new technologies shows promise as a potential mechanism for improving neurological functioning. The results of this study may provide new insights into motor rehabilitation, thereby contributing to the better use of combined tDCS and VR in people with CP.

**Trial Registration:**
ClinicalTrials.gov, NCT04044677. Registered on 05 August 2019.

## Introduction

Cerebral palsy (CP) describes a group of permanent disorders of movement and posture that limit activity. It is attributed to non-progressive disturbances that occur in the developing foetal or infant brain (1). The difficulties that accompany individuals with CP lead to their registration in different and continuous rehabilitation programmes to promote the development of general motor skills, and some studies defend the importance of upper limb tasks to promote physical activity for people with CP. According to Pontén et al. (2) and Sarcher et al. (3), contractions in the upper limbs of individuals with CP start early and require adequate intervention and special attention to provide increases in (or maintenance of) range of movement, better performance and physical activity (especially for the ones with less global mobility), improving the performance of the functions of daily life, increasing independence, activities, and participation (4). Likewise, there is growing evidence of the higher prevalence of metabolic syndrome, cardiovascular disease risk factors, and autonomic nervous system (ANS) dysfunctions in adults with CP (5). According to Katz-Leurer and Amichai (6), because of the sedentary behaviour that results from their limited mobility (i.e., the more limited the mobility, the less activity), individuals with CP are more disposed to chronic disorders such as heart conditions and hypertension.

Thus, considering the presence of musculoskeletal and metabolic conditions in individuals with CP, professionals involved in their care need to consider all the impaired structures and functions and look for proposals for interventions based on scientific evidence that can effectively and comprehensively treat the limitations and restrictions caused by the brain injury (7). To do so, they rely on modern technologies to create new practices and interventions to stimulate different body structures and physiological responses, even for those with more severe conditions, to optimise the acquisition of mo(tor skills, which leads to a more active life (8, 9).

In addition to evidence for the benefits of different techniques for the treatment in rehabilitation of individuals with CP (8–10), recent studies encourage the combination of interventions and technologies as a promising approach for rehabilitation (11). Currently, few studies had investigated the effect of combined therapies in the rehabilitation of individuals with CP, though they presented some encouraging results (12–15). Muszkat et al. (11), suggested that the combination of therapeutic tools should be encouraged to enhance clinical effects and provide more effective and long-lasting results. In this sense, with the increasing accessibility and evolution of technology, virtual reality (VR) and transcranial direct current stimulation (tDCS) have the potential to advance the treatment of CP (10).

The use of VR in rehabilitation is a modern concept of treatment that is based on the use of games and tasks in virtual environments to stimulate physical and cognitive functions in individuals with different types of deficiencies (16, 17). In VR, the user interacts with a three-dimensional environment through remote input devices, such as a keyboard or a mouse (a non-immersive environment), or by more advanced devices (an immersive environment) such as a camera, glasses or special gloves (16). Some studies were carried out using VR in individuals with CP, and the effects were significantly positive concerning the balance and strength of lower limbs (18), learning of general motor skills (19), day-to-day activities (19), and improvement of general learning processes with increased attention in the task (20).

Transcranial direct current stimulation is a non-invasive neuromodulatory technique that produces benefits in the sensorimotor and physiological functions of individuals with different neurological deficits (21), including individuals with CP [see the review by (22)]. The tDCS uses low electrical current (1–2 mA) to modulate the resting potential of neurons below the stimulated site (23). The action mechanism of tDCS is related to the changes in the rates of spontaneous neuronal firing and synaptic and non-synaptic plasticity, whichh influences changes in the resting polarisation of the neurons, and promotes neuroplasticity in cortical areas critically involved in the performance of tasks and in promoting functional benefits (24).

The benefits of tDCS include the flexibility to use it for different activities and exercises (as it presents a mobile characteristic) and the possibility of combining it with other interventions. Spampinato et al. (25) showed that the combination of tDCS with a task using reward characteristics produced neurophysiological modulation of inhibitory networks, and it resulted in enhanced retention of the learned task. Thus, it can be used during fine motor tasks [to reinforce learning of coordinative tasks; (26)], global movements [to increase range of movement; (22)] and physical activities [in order to facilitate motor activities; (12)], and to improve heart and autonomic conditions (27).

Some studies have produced positive results when combining VR and tDCS therapies in stimulating the lower limbs for gait improvement (12) and balance (28, 29). However, no studies have investigated VR and tDCS interventions using an upper limb motor task, which might benefit different clinical conditions of individuals with CP. We organised a triple-blinded, randomised, and controlled crossover trial to investigate the upper limb motor function of individuals with CP with the aims of (1) investigating the effectiveness of the use of tDCS while performing a non-immersive VR task on upper limb motor function and (2) to analysing the influence of a combined VR and tDCS in upper limb motor function through different functional assessment scales, reaction times, and coincident timing analysis, as well as physiological analyses such as heart rate variability.

We hypothesise that all individuals with CP will show an improvement in performance after practising a non-immersive virtual reality task, with benefits in upper limb functional scales, reaction times and, coincident timing analysis underpinned by an adaptation of autonomic neural physiological control after the protocol, and retention of these variables at the 30-day follow-up. However, such improvement and benefits will be more evident after the application of active tDCS than the sham (placebo) tDCS group. If this hypothesis is confirmed, the results of this study will be relevant to the treatment of individuals with CP.

## Methods/Design

We registered this trial on ClinicalTrials.gov (NCT04044677). This paper has been reported in accordance with the Standard Protocol Items: Recommendations for Interventional Trials (SPIRIT) (30) (Figure 1 and Table 1).

**Figure 1 F1:**
[figure not shown]
SPIRIT: Description of the study protocol, schedule of enrolment, interventions, and assessments. ^*^List of specific timepoints in this row.

**Table 1 T1:** Trial characteristics based on WHO Trial Registration Data Set.

**Data category**	**Trial information**
Primary registry and trial identifying number	ClinicalTrials.gov, ID: NCT04044677
Date of registration in primary registry	05 August 2019
Secondary identifying numbers	Ethical Committee of the University of São Paulo, under the number CAAE: 99577318.0.0000.5390
Source(s) of monetary or material support	Coordenação de Aperfeiçoamento de Pessoal de Nível Superior–Brasil (CAPES)
Primary sponsor	University of São Paulo–USP
Secondary sponsor(s)	NA
Contact for public queries	[name], [name]
Contact for scientific queries	[name], [name]
Public title	Virtual reality therapy and transcranial direct current stimulation in cerebral palsy
Scientific title	Effect of combined virtual reality therapy and transcranial direct current stimulation on children and adolescents with cerebral palsy
Country of recruitment	Brazil
Health condition(s) or problem(s) studied	Cerebral palsy
Interventions	Group 1 will start with 10 sessions of active tDSC combined with VR tasks. After a 1 month washout, this group will be reallocated to another 10 sessions with sham tDCS combined with VR tasks. Meanwhile, group 2 will carry out the opposite protocol (i.e., participants will start an allocated 10 sessions of sham TDCS combined with VR tasks, and after a 1 month washout period will be reallocated to 10 sessions of active tDCS combined with VR tasks).
Key inclusion and exclusion criteria	Inclusion criteria: the agreement to participate in the research from themselves and their legal guardians; a clinical diagnosis of CP will be performed by a neuropaediatric clinician; with Gross Motor Function Classification System (GMFCS) levels I to IV; and Manual Ability Classification System (MACS) I to IV; age range 4–14 years. Exclusion criteria: do not understand the tasks; motor difficulties that impede the completing of the virtual tasks; cardiac diseases that impede the assessment of heart rate variability (HRV) and surgery; use of an upper limb spasticity inhibitor during the previous 6 months; metal prosthesis on the head. Withdrawal criteria: participants will be withdrawn from the study if they are not willing to continue cannot be present on the day of the experiment, or miss two treatment sessions.
Study type interventional allocation	Randomised
Masking	Triple-blinded
Assignment	Crossover
Primary purpose	Treatment
Date of first enrolment	March 2019
Target sample size	35
Recruitment status	Recruiting
Primary outcome(s)	Motor skills improvement
Key secondary outcome(s)	HRV improvement

### Overview of the Study Design

A triple-blinded randomised controlled crossover trial with a 1:1 allocation ratio will be conducted, and all participants will undertake non-immersive VR tasks and active or sham tDCS. Groups A–S will start with 10 daily sessions of tDCS-active combined with VR tasks for 20 min. After a 1 month washout, this group will be reallocated to another 10 daily sessions of 20 min with sham tDCS combined with VR tasks. Meanwhile, groups S–A will carry out the opposite protocol (participants will start an allocated 10 sessions of sham tDCS combined with VR tasks, and after a 1 month washout period will be reallocated to 10 sessions of active tDCS combined with VR tasks). The 1 month washout period has been used and was shown to be sufficient to reset the effects of the first 10 sessions in Biabani et al. (31). Figure 2 summarises the planned experimental design. This research protocol follows the SPIRIT recommendations.

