**Figure 2 F2:**
[figure not shown]
Study design. MACS, Manual Ability Classification System; GMFCS, Gross Motor Function Classification System; PEDI, Pediatric Evaluation of Disability Inventory; VR, virtual reality; n: sample size; tDCS, transcranial direct current stimulation; D0-D11, days of interventions in which D0 is the baseline, D1 to D10 are the days of interventions and the D11 is the day of the final assessments. Participants and sampling.

Thirty-six participants will be recruited through referral by the coordinators of three clinics in Brazil: *Intensiva, Intertherapy*, and *Therapies*, located in São Paulo state. Those interested in participating will undergo a detailed screening using the eligibility criteria for enrolment in the study.

The sample size was calculated using statistical software (GPower 3.1.5) on the main outcome measure (i.e., the motor score). This calculation was based on data from one study with a group of individuals with CP who received tDCS (32). The power was 0.80; the alpha was 0.05; and the effect size was 0.65 (Cohen's d). The sample estimation indicated that 28 participants would be necessary (i.e., 14 per group). With an adjustment to allow for a withdrawal rate (20%), we will recruit 36 participants.

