### VR Task for Assessment

We will use two VR tasks to assess the participants' capacity and improvement with intervention. The tasks will be used as assessment at three points: initial assessment (D0); assessment after 5 sessions (D5); and final assessment (D11).

The assessment tasks are presented below:

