### Assessments for Primary Outcome

The VR task will be used to assess the participants' motor abilities (accuracy, precision, and trend of anticipation or delay in movement) during each intervention. Also, we will use coincident timing and reaction time tasks, ABILHAND-Kids, ACTIVLIM-CP, and visual and cognitive assessments to characterise the group and to find influences on motor improvement by using correlation tests. These tests will be carried out at three stages: initial assessment (D0); assessment after five interventions (D5) and final assessment (D11) (Figure 1).

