## Discussion

Although treatment with tDCS is feasible and effective, further studies with individuals with CP are essential for a better understanding of the motor and autonomic effects of treatment with VR associated with tDCS for clinical practice. Therefore, we organised this study to analyse the influence of combined therapy of VR and tDCS for children and adolescents with CP, with VR tasks for upper limb and trunk movements. As outcome measures, we chose different upper limb functional assessment scales, computer tasks for the analysis of reaction time and anticipatory timing, as well as physiological analyses such as heart rate variability (HRV). Considering our hypothesis, supported by previous studies using similar tasks (8, 68, 70, 71), we speculate that all individuals with CP will show an improvement in performance during therapy sections and will maintain this improvement in follow-up assessments (15 and 30 days). We also hypothesise that the individuals using active tDCS with present better results.

The results from this study can positively influence the rehabilitation programs and provide answers to four important topics:

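### The crossover relies on a 1-month reset while the hypothesis expects gains to last 30 days; carry-over could bias the active-sham contrast, in a direction that depends on baseline handling the text does not fix

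*Protocol article*

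**What the plan says.** **Washout.** Under Overview of the Study Design, the article says of the interval between periods: "The 1 month washout period has been used and was shown to be sufficient to reset the effects of the first 10 sessions".

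**Retention.** The hypothesis at the end of the Introduction expects all participants to improve with VR practice, and adds "retention of these variables at the 30-day follow-up". The next sentence says that "such improvement and benefits will be more evident after the application of active tDCS than the sham (placebo) tDCS group". The Discussion expects that participants "will maintain this improvement in follow-up assessments (15 and 30 days". One place therefore names one follow-up time and the other names two.

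**Schedule.** The section VR Task for Assessment lists "initial assessment (D0); assessment after 5 sessions (D5); and final assessment (D11". Assessments for Primary Outcome gives the same three stages. The Figure 2 legend states that "D0 is the baseline, D1 to D10 are the days of interventions and the D11 is the day of the final assessments". The Abstract says that evaluations take place at baseline, during and after active and sham stimulation. This suggests a D0 in each period, but the text does not say so.

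**Outcome and analysis.** Primary Outcome defines the result as change from baseline, without saying which baseline applies in period 2. Statistical Analysis mentions follow-up for HRV without giving days, and names no period or carry-over term.

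**The concern.** The end of a 1-month washout and a 30-day follow-up after period 1 are practically the same moment. The design needs the first period's effects to be gone by then, and the hypothesis needs them to be present.

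Only part of what is retained matters for the treatment comparison. VR learning that persists equally in both sequences is a period effect, and drops out once period is modelled. A benefit specific to active stimulation does not drop out: it enters the sham period of the active-first group and has no counterpart in the sham-first group. That is differential carry-over, and it acts on the trial's main contrast.

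The retention hypothesis is itself at stake. After period 1, the 30-day point can only be the start of period 2. After period 2, the text describes nothing later than D11.

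**Working it through.** **Inputs from the article** (Participants and sampling): effect size 0.65 (Cohen's d), alpha 0.05, power 0.80, 28 participants before withdrawals (14 per group), 36 recruited.

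**The plan's own figure.** At d = 0.65, a two-sided paired t-test needs 21 participants in total and a two-sided two-sample t-test needs 39 per group. Neither gives 28. A total of 28 results if 0.65 is scaled by the between-person SD and a within-person correlation of 0.3 is assumed, which the article does not state. The power figures below therefore rest on an assumption: 0.65 is read as the paired standardised effect (dz), with 28 completers. The contradiction does not depend on this.

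**Set-up.** Let tau be the true active-sham difference, and assume additive effects. Write A1, S1, A2 and S2 for the active and sham means in periods 1 and 2. The crossover estimate, free of period effects, is

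0.5 × [(A1 - S1) + (A2 - S2)].

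In period 2 the sham result comes from the active-first group. Let that group still hold c0·tau of extra benefit at the period-2 D0, and c1·tau at the period-2 D11.

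**Case 1: end-of-period scores, or change from the initial D0.** S2 is raised by c1·tau. Writing c for c1, the estimate is 0.5 × [tau + (tau - c·tau)] = tau(1 - c/2).

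**Case 2: change from each period's own D0.** The sham change in period 2 is shifted by (c1 - c0)·tau, so the estimate is tau × [1 + (c0 - c1)/2].
- Benefit persists through period 2 (c1 = c0): tau, unbiased.
- Benefit present at D0 but gone by D11 (c1 = 0, c0 = c): tau(1 + c/2), inflated.

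**Numbers.** The article gives no value for c, so the whole range is shown. The power and N columns apply to Case 1 (two-sided paired t-test).

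| c | Case 1 factor | Expected dz | Power, n = 28 | N for 80% power | Case 2 factor if benefit fades fully |
|---|---|---|---|---|---|
| 0 | 1.000 | 0.650 | 0.91 | 21 | 1.000 |
| 0.25 | 0.875 | 0.569 | 0.83 | 27 | 1.125 |
| 0.5 | 0.750 | 0.488 | 0.70 | 35 | 1.250 |
| 0.75 | 0.625 | 0.406 | 0.54 | 50 | 1.375 |
| 1 | 0.500 | 0.325 | 0.38 | 77 | 1.500 |

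At c = 0.5, the same carry-over gives an expected 0.65 × 0.75 = 0.49 in Case 1 and up to 0.65 × 1.25 = 0.81 in Case 2.

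**Period 1 alone.** This comparison is free of carry-over. With 14 per group and 0.65 read as a between-group d, two-sided power is 0.38, before any gain from baseline adjustment.

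**The case against.** **The two statements may concern different things.** The reset could refer to stimulation effects only, and the retention to VR learning in everyone. The Discussion places maintenance and active superiority in separate sentences, and no sentence says outright that the active-sham difference lasts 30 days. This has some weight. But the Introduction names retention among the expected benefits and then says at once that these will be more evident after active stimulation. An active-specific benefit at 30 days is the natural reading, and the reset statement covers the effects of all ten sessions, which combine stimulation and VR.

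**A reader might infer that retention necessarily shrinks the contrast.** The documents do not support that. Shrinkage belongs to Case 1, and the text does not fix the baseline. With a D0 in each period, which the Abstract suggests, the bias may be nil or upward.

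**A reader might infer that nothing is measured after period 2, or that retention cannot be examined at all.** Neither follows. D11 is a post-treatment assessment, and the period-2 D0, if taken, gives a 30-day comparison for period 1. What the text lacks is a retention visit beyond D11 for period 2. Figures 1 and 2 are not shown and may list one.

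**A reader might conclude that the reset claim is false.** Its cited source is not available here, so the claim can be reconciled with the hypothesis but not refuted.

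**The size is conditional.** In Case 1, c is the fraction left at the period-2 D11. That is a month plus ten weekday sessions after period 1, so retention at 30 days does not fix its value.

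**Period terms and sensitivity analyses often sit in an SAP that is not shown.** Their absence is not the finding. An SAP could handle carry-over, but it would not remove the conflict between the article's own statements.

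**Conclusion.** The concern holds as a conflict between the design's key assumption and the trial's own hypothesis, with possible bias of undetermined direction. If a fraction c of the active-specific benefit persists, the expected contrast can lie anywhere from tau(1 - c/2) to tau(1 + c/2), depending on the baseline used and on whether the benefit persists or fades during period 2. At c = 0.5 that is 0.49 to 0.81 around a true 0.65. In the shrinking case, power with 28 completers is 0.70 instead of 0.91. These figures assume additive effects, 0.65 as a paired effect, and a c that no document gives.

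The follow-up times are also inconsistent (30 days against 15 and 30 days), and neither appears in the schedule as described in the text.

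**What to change.** 1. Reconcile the washout statement in Overview of the Study Design with the retention statements in the Introduction and Discussion, and stop treating complete reset as established.
2. State that D0 is repeated before period 2. Include a period term, name the baseline used in each period, and state the carry-over bias that comes with it: shrinkage for end-of-period scores or change from the initial D0, possible inflation for change from each period's own D0.
3. Compare the active-first and sham-first groups at the period-2 D0, adjusted for the period-1 D0. Report this as both the 30-day retention result and the carry-over estimate.
4. Always report a baseline-adjusted period-1-only comparison as a prespecified sensitivity estimate. Do not use a carry-over test to choose between analyses.
5. Limit the retention claim to the comparison in item 3. Align the follow-up times, and remove the 15-day claim unless the schedule lists that visit.

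**Cost.** Changes of wording and two additional analyses, with no new data provided D0 is already repeated before period 2. The drawback is precision: the period-1 comparison has about 38% power at d = 0.65 with 14 per group, so it indicates how robust the crossover result is and cannot replace it.
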